### Economic evaluation

#### Primary objective

Our primary economic aim is to examine whether delivering the eHealth PPI to patients during the waiting period and their loved ones, followed by a subsequent mental health treatment for patients, is more cost-effective from a societal perspective, compared to TAU. We hypothesize that offering this eHealth PPI to participants in conditions 1 and 2, followed by a mental health treatment, is cost-effective from a societal perspective, compared to condition 3 (TAU).

#### Secondary objective

Our secondary economic aim is to evaluate whether involving loved ones in the eHealth PPI during the waiting period, followed by a mental health treatment for patients, will yield additional cost-effectiveness benefits from a societal perspective, compared to only involving patients. We anticipate that involving loved ones in condition 2 of the eHealth PPI, followed by a mental health treatment for patients, will be cost-effective from a societal perspective, compared to condition 1.

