In most cases, the patient’s loved ones (e.g., partner, family, friends, colleagues) are not involved in treatment, even though it is well established that interpersonal connections, such as connections with loved ones, may further promote patient recovery [25]. Furthermore, research suggests that positive activities could promote positive relationships with others, which may mitigate interpersonal risk factors like loneliness [19]. Importantly, loved ones often become caregivers for patients, which may cause them to feel burdened. Consequently, loved ones may experience mental health complaints as well, requiring more demand for psychological care [26]. The effects of psychological interventions may be enhanced by involving the patient’s social network, as this may yield synergistic effects that strengthen an intervention’s overall impact [27]. Hence, PPIs targeting both patients and their loved ones may enhance patient recovery and yield positive effects among loved ones who may also experience mental health complaints.

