#### Measuring quality adjusted life years for the CUA

In the CUA of study 2, new outcome measures will be collected, including scores on the EuroQol 5-Dimension 5-Level questionnaire (EQ-5D-5L) [78, 79]. The EQ-5D-5L will be used to derive Quality Adjusted Life Years (QALYs), which is defined as the primary outcome in the CUA. The EQ-5D-5L questionnaire is primarily used to assess quality of life in either the general population or subpopulations facing debilitating illness. Given the absence of subscales, the EQ-5D-5L includes 5 items encompassing 5 dimensions related to quality of life: mobility, self-care, daily activities, pain/discomfort, and anxiety/depression. These items are measured ordinally using a same-day recall period, with multiple-choice responses ranging from ‘’no problems’’ to ‘’extreme difficulties’’. With Gwet’s Agreement Coefficient ranging from 0.64 to 0.97 for the 5 dimensions, a Dutch version of the EQ-5D-5 L was considered reliable [80]. However, the clinical meaning of EQ-5D-5 L scores in patients facing mental health complaints has been criticized [81].

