#### Measuring societal costs for the CEA and CUA

In both the CEA and CUA, costs will be measured among patients from a societal perspective, including healthcare costs (i.e., health services use and medications), productivity losses (i.e., absenteeism and presenteeism), and intervention costs (i.e., the costs of implementing the intervention). To measure healthcare costs and productivity losses, a 3-month recall period will be used. Consumption of health services, medications, and productivity losses in patients facing psychological complaints will be measured, using the Treatment Inventory of Costs in Patients with psychiatric disorders (TIC-P) [87].

By definition, the TIC-P was developed as a generic questionnaire to estimate societal costs across all Dutch adult mental health populations within inpatient and outpatient clinical settings. Using both categorical multiple choice and numerical open ended questions, the TIC-P aims to measure 3 subscales: general demographics (7 items), healthcare consumption (38 items), and productivity losses in both the formal and informal workspace (12 items) [87]. In the absence of subscale estimates (e.g., Cronbach’s alpha) on reliability, Cohen’s Kappa was still considered highly satisfactory for most separate items on healthcare consumption, and satisfactory for most items on productivity losses [88]. Productivity losses in the workspace are based on absenteeism (i.e., not being able to work) and presenteeism (i.e., reduced productivity in the workspace). Informal productivity losses related to unpaid work will also be measured. Patients will report their hours of absence (i.e., absenteeism) and the additional hours they needed to finish work due to health complaints (i.e., presenteeism).

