Clinical profile	*x*						
Demographics	*x **						
Expectations	*x **						
PHQ-9	*x**	*x**					
RSS	*x **	*x **					
TIC-P	*x*	*x*	*x*	*x*	*x*	*x*	*x*
EQ-5D-5 L	*x*	*x*	*x*	*x*	*x*	*x*	*x*
MHQoL	*x*	*x*	*x*	*x*	*x*	*x*	*x*
ICECAP-A	*x*	*x*	*x*	*x*	*x*	*x*	*x*
LOT-R	*x **	*x **					
SCS-SF	*x **	*x **					
SBI	*x **	*x **					
GQ-6	*x **	*x **					
BRS-NL	*x **	*x **	*x*	*x*	*x*	*x*	*x*

*x* = patient; ***= loved one; MHC-SF = Mental Health Continuum – Short Form; BSI = Brief Symptom Inventory; SUS = System Usability Scale; Post-module process questions = questions related to the performance of each PPI module from a process evaluation perspective; Clinical profile = mental health complaints, symptomatic severity; Demographics = sex, age, income, education; Expectations = participant expectations regarding the eHealth PPI; PHQ-9 = Patient Health Questionnaire – 9; RSS = Relational Satisfaction Scale; TIC-P = Treatment Inventory of Costs in Patients with psychiatric disorders; EQ-5D-5 L = EuroQol 5-Dimensions 5-Levels; MHQoL = Mental Health Quality of Life; ICECAP-A = ICEpop CAPability measure for Adults; LOT-R = Life Orientation Test – Revised; SCS-SF = Self-Compassion Scale – Short Form; SBI = Savoring Beliefs Inventory; GQ-6 = Gratitude Questionnaire – 6; BRS-NL = Brief Resilience Scale – Netherlands

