In the second RCT arm, both patients and their loved ones will have an individual user account to engage with the eHealth PPI. Hence, total intervention costs of this eHealth PPI condition (arm 2) are expected to outweigh those of the patient-only eHealth PPI condition (arm 1). All healthcare, non-healthcare and intervention cost components will be indexed to the most recent base year, using the latest costing manual in Dutch healthcare [66]. If necessary, all estimated costs will be extrapolated to an extended time horizon that is not covered by the 3-month recall period. Following the ITT-principles throughout the entire RCT duration, the total sum of healthcare costs, non-healthcare costs, and intervention costs will be calculated and averaged per participant within each RCT condition, yielding an estimate of the average societal cost per RCT condition. These estimates will then allow for comparative base-case analyses of cost-effectiveness.

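### Arm 2's economic results are called societal, but they charge the loved ones' programme cost and measure none of their health, care use, productivity or time

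*Protocol article*

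**What the plan says.** The secondary objective under Economic evaluation asks whether involving loved ones "will yield additional cost-effectiveness benefits from a societal perspective, compared to only involving patients", and anticipates that arm 2 "will be cost-effective from a societal perspective, compared to condition 1". The primary economic objective also compares arm 2 with TAU from a societal perspective.

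On cost, Valuation of societal costs states that in arm 2 "both patients and their loved ones will have an individual user account to engage with the eHealth PPI", and for that reason expects arm 2's intervention cost to exceed arm 1's. Measuring societal costs for the CEA and CUA says that "costs will be measured among patients from a societal perspective", using the TIC-P.

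On effect, QALYs come from the EQ-5D-5L, with MHQoL and ICECAP-A in a sensitivity analysis. Table 2 marks all three, and the TIC-P, for patients only at all seven time points. Loved ones complete the MHC-SF, BSI and BRS-NL at T0 and T1 only.

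On rationale, the Background gives two possible benefits of treating both people: better patient recovery, and that the intervention may "yield positive effects among loved ones who may also experience mental health complaints". The Discussion repeats both.

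**The concern.** The loved one is a treated person in arm 2. The programme delivered to that person enters the cost difference, but nothing that happens to that person's health enters the effect difference. Nor do the loved one's care use and productivity enter the costs, although the Background says loved ones' complaints can raise demand for psychological care. One of the two stated reasons for arm 2 is therefore invisible to the evaluation that is meant to judge it.

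At stake is the conclusion on adding loved ones. The base-case section plans an ICER for arm 2 against TAU and a CEAC probability for arm 2 against arm 1. A reader will take either as the societal value of adding a loved one. The limitations in the Discussion and in the Appendix do not mention the exclusion. A later analysis plan cannot repair it, because the article fixes who completes which instrument, and utilities that were not collected cannot be recovered.

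**Working it through.** **The plan's own figures.** 207/(1 − 0.355) = 320.9, so 321 patients; 321/3 = 107 per arm; 321 + 107 loved ones = 428. The cap is 408 + 136 = 544. The Appendix shortfall is (27.52 − 20.5)/27.52 = 0.255, stated as 0.26, which leads to the EUR 20,000 threshold. All of these reproduce.

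**What is counted for the 107 loved ones in arm 2:**

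| Item | In the arm 2 result? | Where |
|---|---|---|
| Programme cost (second account) | Yes | Valuation of societal costs |
| QALYs (EQ-5D-5L; MHQoL, ICECAP-A) | No | Table 2 |
| Health-care use, productivity (TIC-P) | No | Table 2; Measuring societal costs |
| Time on the programme | No | Not among the listed cost categories |
| MHC-SF, BSI, BRS-NL (CEA effects) | T0 and T1 only; no stated use in the CEA | Table 2 |

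Loved ones take part only in arm 2, so their MHC-SF, BSI and BRS-NL scores cannot form an incremental effect against arm 1 or arm 3.

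**Size on the counted items.** Let c be the extra arm 2 cost per dyad against arm 1, dP the patient QALY difference, dL the loved-one QALY gain and W the willingness to pay.

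- As planned: NMB = W × dP − c.
- With loved-one health: NMB = W × (dP + dL) − c.
- Difference: W × dL. At W = EUR 20,000 and dL = 0.01, this is EUR 200 per dyad.

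The documents give no account cost and no QALY effect, so c, dP and dL below are assumptions. A utility gain of 0.02 for 3 months is 0.02 × 0.25 = 0.005 QALY (EUR 100). A gain of 0.03 for 12 months is 0.03 QALY (EUR 600).

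| c (EUR) | dP | dL | ICER / NMB as planned | ICER / NMB with dL |
|---|---|---|---|---|
| 50 | 0.005 | 0.005 | 10,000 / +50 | 5,000 / +150 |
| 200 | 0.005 | 0.010 | 40,000 / −100 | 13,333 / +100 |
| 400 | 0.005 | 0.010 | 80,000 / −300 | 26,667 / −100 |

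Only the middle row crosses EUR 20,000.

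**The item that works the other way.** The intervention section asks about 4 hours per week over eight weeks: 4 × 8 = 32 hours per loved one. At an assumed EUR 10 to 40 per hour this is EUR 320 to 1,280, equivalent to 320/20,000 = 0.016 up to 1,280/20,000 = 0.064 QALY. In the middle row, the lowest time value turns +100 into 100 − 320 = −220.

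**Break-even loved-one gain**, (c − W × dP)/W, for dP = 0.005:

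- c = 200: at W = 20,000, (200 − 100)/20,000 = 0.005; at W = 50,000, (200 − 250)/50,000 is negative, so no gain is needed.
- c = 400: at W = 20,000, (400 − 100)/20,000 = 0.015; at W = 50,000, (400 − 250)/50,000 = 0.003; at W = 80,000, (400 − 400)/80,000 = 0.

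**The case against.** A reader might infer that the plan is biased against arm 2 and could wrongly reject it. The documents do not support that, for five reasons, all of which stand.

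- **Direction.** Only programme cost is charged for loved ones. Their time is left out, which favours arm 2 and on the assumed values can exceed the omitted health gain. Their care use and productivity are also left out and could go either way. In addition, costs are to be averaged per participant: if arm 2's total were divided by 214 people instead of 107 patients, its mean cost would roughly halve.
- **No accept-or-reject rule.** ICERs are planned against TAU only. Arm 2 against arm 1 appears as a CEAC probability over EUR 0 to 80,000, and the clinical comparison of these two arms is labelled exploratory.
- **Rationale.** The Background says loved ones may benefit. Any gain that reaches patients through a loved one is captured by the patient instruments, so one of two reasons is missed, not both.
- **Threshold.** EUR 20,000 was derived from the shortfall of a mental-health patient population. Applying it to loved ones' QALYs is an assumption.
- **Size.** Every reversal rests on assumed costs and effects, and two of the three worked rows do not reverse.

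These points limit the claim about direction. They do not remove the mismatch between the societal label and what is measured. Each further uncounted item makes that label less accurate.

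**Conclusion.** The arm 2 results are not a full societal evaluation. They include loved-one programme cost and exclude loved-one health, care use, productivity and time. For the CUA this is certain from Table 2. For the CEA it follows because loved-one scores stop at T1, have no comparator and are given no role.

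On programme cost and QALYs alone, the omission lowers arm 2's net benefit by EUR 200 per dyad for each 0.01 loved-one QALY, if EUR 20,000 is accepted for loved ones. Once uncosted time is considered the net direction is unknown. That the exclusion would change the cost-effectiveness result is possible but not shown, since the documents give neither an account cost nor a QALY effect. What the design can support is a statement about adding loved ones as judged by patient outcomes.

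**What to change.** 1. In both economic objectives and in Cost-effectiveness: base-case analyses, state that arm 2 results include loved-one programme cost but exclude loved-one health, care use, productivity and time. Do not present them as a full societal result, and list the exclusion among the limitations.
2. Report arm 2 with and without the loved-one programme cost, per dyad.
3. Report the break-even loved-one QALY gain per dyad, (extra cost − WTP × extra patient QALY)/WTP, over the planned WTP range above zero. Note beside it that EUR 20,000 was derived for patients and that loved-one time is uncosted.
4. Limit conclusions on adding loved ones to patient outcomes, in either direction, with no special protection against a negative finding.

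Adding the EQ-5D-5L for loved ones at T0 and T1 would not solve this: it would give an uncontrolled change that ends at programme completion, not an incremental QALY gain.

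The cost is protocol wording and two calculations on data already planned, with no change to randomization, sample size, visits or the primary clinical analysis. The downside is a more qualified conclusion for arm 2.

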### Implementation procedures

Our aim is to explore the acceptability, feasibility, engagement, adherence, and accessibility of the proposed eHealth PPI from a user-perspective.

## Methods

### Study designs

Two study designs will be developed. While study 1 will employ a replicated single case design (RSCD) to assess the preliminary intervention effects and procedural implementation of the proposed eHealth PPI, study 2 will conduct a randomized controlled trial (RCT) to examine the eHealth PPI more robustly in terms of clinical effectiveness, cost-effectiveness and procedural implementation.

#### Study 1: replicated single-case design

A pilot study employing a replicated single-case design (RSCD) will be conducted to examine the implementation procedures of the eHealth PPI from a user-perspective, focusing on: acceptability, feasibility, engagement, adherence, and accessibility. Following study enrollment, the RSCD will include ten participants (five patients and five loved ones) completing multiple measurements. These measurement phases include: pre-measurement, interim measurement after each intervention module, and a post-measurement. The dependent primary outcome variable to be measured is positive mental health, which consists of social, emotional, and psychological wellbeing [41]. Dependent secondary outcome variables include optimism, self-compassion, savoring, gratitude, resilience, and quality of life. Generally, an RSCD allows for the early identification of potential facilitators and barriers to intervention implementation, which may be used to inform adjustments to the intervention design and materials [42]. A total study time of 10 weeks is estimated for the participants.

#### Study 2: randomized controlled trial design

A three-arm RCT design will be implemented to examine the (cost-)effectiveness and procedural implementation of the eHealth PPI for patients awaiting mental health treatment without loved ones (arm 1) and in patients awaiting mental health treatment with their loved ones (arm 2), compared to patients not receiving the eHealth PPI during their waiting period for mental health treatment (TAU in arm 3). Following study enrollment, all participating patients will be assigned to one of the three RCT arms, using simple randomization with an equal 1:1:1 allocation ratio. A loved one will be added to each patient in arm 2. Participants will receive seven different measurements: a pre-PPI measurement, immediate post-PPI measurement, 3-month post-PPI measurement, 6-month post-PPI measurement, 9-month post-PPI measurement, 12-month post-PPI measurement and a final 12-month measurement following treatment completion at a Dutch mental health clinic. The dependent primary outcome variable will be positive mental health, which consists of social, emotional, and psychological wellbeing [41]. Dependent secondary outcome variables include optimism, self-compassion, savoring, gratitude, resilience, quality of life and costs in psychiatric patients. Independent background characteristics include demographics (e.g., age, sex, education), clinical profile (e.g., severity of complaints) and expectations. A flowchart of the RCT is presented in Fig. 1 on page 13 below, displaying the primary and secondary outcomes for each measurement.

**Fig. 1 Fig1:**
[figure not shown]
Flowchart of the proposed RCT (study 2). Note: *Predicted start of the official intake and a mental health treatment for most patients: Although the official intake and treatment could take place in principle after the pre-measurement, most patients will likely receive treatment more than 5 weeks after completion of the first post-measurement due to long waiting times in Dutch mental healthcare (i.e., > 14 weeks)

### Study population

The study population will consist of Dutch patients facing a range of mental health symptoms and their loved ones. While the participating outpatient mental health clinic (i.e., Lionarons GGZ) does not provide treatment for acute suicidality and psychotic complaints, the most common clinical diagnoses of patients waiting for general or specialized mental healthcare at this clinic are depression, post-traumatic stress disorder, anxiety, personality disorders and developmental disabilities (e.g., autism spectrum disorder). The outpatient mental health clinic will be supported by Embloom, which is an eHealth organization identifying provisional diagnoses and care needs of incoming patients. In principle, loved ones are broadly defined as all individuals who are meaningfully connected to a patient [25]. This definition acknowledges the patient’s autonomy in deciding who qualifies as a meaningful connection (e.g., a formal partner, blood-related family member, close friend, or colleague). Hence, the current project may include a diverse range of valuable interactions between patients and their loved ones, which may increase the likelihood of patient inclusion. The anticipated research population will probably contain a broad spectrum of mental health diagnoses and vulnerable target groups.

Patients and their loved ones are eligible for both studies if they meet the following inclusion criteria during the recruitment procedure: all participants [1] are at least 18 years old, [2] are able to read and speak the Dutch language, and [3] have access to the internet. In addition, patients [4] have obtained an referral for treatment at the outpatient mental health clinic and [5] are able to appoint an adult loved one willing to participate. Patients will be excluded if they meet one of the following two criteria during the recruitment procedure: [1] the patient is referred back to their general practitioner by the eHealth organization supporting the outpatient mental health clinic, [2] the patient meets the criteria for severe acute suicidality or psychotic symptoms.

### Sample size

#### Study 1 (RSCD): sample size considerations

A small sample of ten participants will be included in study 1, comprising five patients and five loved ones, before scaling up to a fully powered trial. Using a replicated single-case design (RSCD), measuring a few single cases (*n* = 1) of patients and loved ones repeatedly is usually sufficient to examine relevant aspects of intervention implementation. In study 1, single cases will be followed over a prolonged period of time using repeated measurement phases prior to, during, and after the RSCD. Although the data obtained may have limited implications for group-level analysis, these measurement phases enable short-term detection of implementation experiences on the individual level, making the RSCD a relatively efficient design for small pilot studies [43, 44].

#### Study 2 (RCT): adaptive sample size design

An adaptive sample size design will be employed in study 2, estimating the required sample size prior to the study (the a priori sample size) that will be re-estimated during the trial. The proposed re-estimation will be based on results of interim analyses (the re-estimated sample size). This adaptive element in the design of study 2 is motivated by uncertainty in the anticipated effect size and dropout rate. If the actual effect size in the interim analysis is substantially different from the a priori assumed effect size, the a priori estimated sample size may be inadequate to achieve the desired level of statistical power in decision-making. Therefore, interim analysis will be applied to (a) reassess the adequacy of the a priori computed effect size; (b) reassess the initially assumed dropout rate; and (c) replace the a priori sample size by a re-estimated sample size based on these reassessed parameters if needed.

#### A priori sample size

The a priori sample size in study 2 is based on the anticipated change in positive mental health between baseline and one-year treatment follow-up at the clinical setting in the intervention conditions compared to the control group. Compared to arm 3 (i.e., TAU), a medium effect size of Hedges’ g = 0.45 is assumed for both PPI arms followed by a mental health treatment (i.e., arms 1 and 2). The effect size of Hedges’ g = 0.45 is conservatively estimated based on prior studies about PPI effectiveness [21, 45], assuming an overlap in treatment mechanisms when combining a PPI with a subsequent mental health treatment. The Mental Health Continuum – Short Form (MHC-SF) is defined as the primary outcome [46], which is justified in the section on ‘’Data collection’’. Using a pretest-posttest design for this primary outcome, the required sample size was estimated at 207 patients, including 69 patients per treatment arm under a 5% Type I error rate, 80% statistical power, and an equal allocation ratio. While the PPI + mental health treatment arm including loved ones (arm 2) is expected to yield a larger effect size than the PPI + mental health treatment arm without loved ones (arm 1), the actual difference between both effect sizes is unknown due to the novelty of the inclusion of loved ones. In the absence of previous studies, we will conservatively assume identical effect sizes for both arm 1 and arm 2, which can be compared to arm 3 (TAU) with a sufficient degree of certainty. In addition, we still aim to compare arm 1 to arm 2 exploratively, knowing that these specific comparisons may not be adequately powered. Assuming a 35,5% attrition rate between baseline and the 1-year follow up measurement following treatment completion based on previous findings [47, 48], a total sample size of 207/(1–0.355) = 321 participants (*n* = 321) is required, yielding 107 patients per treatment arm. Since the second arm involves one loved one per patient, this arm will contain 214 participants. Thus, a total sample size of 428 participants will be required, including 321 patients and 107 loved ones.

